### Experimental intervention

The experimental intervention in this study is PBT. The aim of this training program is to improve reactive balance control in older adults by practicing balance recovery from unexpected perturbations in a safe and controlled environment.

#### Training setup

Training will take place on the CAREN system at the MUMC+ department of physical therapy. The CAREN is a dual-belt treadmill system embedded in a motion platform with 6 degrees of freedom and surrounded by a 180 degree screen. The treadmill and the motion platform can both provide reactive balance challenges separately or combined, providing a wide array of possible types and directions of perturbation. Virtual reality environments are projected onto the screen to make the training activities more immersive. Subjects will wear a safety harness at all times during training to protect them from injuries in case of an unsuccessful balance recovery.

#### Training dose

Based on previous studies, we hypothesize that three training sessions of 30 min each will be enough to facilitate adaptation of reactive balance control [32, 34–36, 39–41].

#### Perturbation intensity and progression

While it is not clear exactly how perturbation magnitude impacts motor learning and retention, it appears that high-magnitude perturbations (where the subject initially needs the safety harness to recover their balance) result in fast and significant adaptation with long-term skill retention [28]. However, with regard to the safety and acceptability of training, a more progressive and personalized approach that is still challenging seems more reasonable. We therefore decided to monitor how challenging the training is for each subject, and to individualize the progression of difficulty levels. With this goal in mind, we will use a numeric rating scale (NRS) where each subject will rate the difficulty of maintaining balance control during training on a scale from 1 to 10. The following guideline will be used to interpret how challenging the training is for each subject; NRS 1–3 barely challenging, NRS 4–5 mildly challenging, NRS 6–7 challenging, NRS 8–9 very challenging, NRS 10 unsuccessful balance recovery. The NRS scale will be monitored regularly during training, with the aim to train at an NRS of 6 to 9. If a subject scores the level of challenge as below 6 and this score is consistent with the subjective impression of the physical therapist, the perturbation difficulty level will be increased. The maximum perturbation difficulty levels displayed in Tables 3, 4, 5 and 6 are based on the possibilities of the CAREN system, and on pilot testing with healthy older adults.

**Table 3 Tab3:** Perceived difficulty scores, according to the NRS score and their corresponding increase in difficulty level

NRS score (0–10)	Increase in difficulty level (percentage)
1	15%
2	15%
3	15%
4	10%
5	10%
6	5%
7	5%
8	0%
9	0%
10	0% or decrease by 5–10%

*NRS score* Numeric Rating Scale score. Increase in difficulty level: The percentage by which the difficulty level will be increased if the subject scores the corresponding NRS score

**Table 4 Tab4:** Difficulty levels and their corresponding perturbations of platform displacement and maximum speed of shift

Difficulty level	Displacement (cm)	Maximum speed (m/s)
1	5	0.11
2	7.5	0.16
3	10	0.21
4	12.5	0.26
5	15	0.31
6	17.5	0.36
7	20	0.41

Displacement: The distance in centimeters which the platform will move during a perturbation of a certain level. Maximum speed: The maximum speed at which the corresponding platform displacement will be reached

**Table 5 Tab5:** Difficulty levels and their corresponding perturbations of platform angles and maximum speed of the platform tilt

Difficulty level	Tilt left/right (degrees)	Tilt forward/backward (degrees)	Speed (degrees/s)
1	3	2	6.2
2	4.5	3.5	9.2
3	6	5	12.2
4	7.5	6.5	15.2
5	9	8	18.2
6	10.5	9.5	21.2
7	12	11	24.2

Tilt: The number of degrees by which the platform will tilt to a certain side during a perturbation of the corresponding level. Speed: The maximum speed at which the corresponding platform tilt will be reached

**Table 6 Tab6:** Difficulty levels and their corresponding perturbations of treadmill belt acceleration/deceleration, speed (increase) and duration of unilateral treadmill acceleration and deceleration

Difficulty level	Acceleration/Deceleration (m/s^2^)	Speed (increase/decrease, m/s)	Duration (s)
1	3	0.5	0.20
2	3	0.85	0.28
3	3	1.2	0.36
4	3	1.55	0.44
5	3	1.9	0.52
6	3	2.25	0.60
7	3	2.5	0.68

Speed: The increase or decrease in unilateral treadmill belt speed in m/s for each difficulty level. Duration: The amount of time during which the increased speed is maintained

#### Perturbation types

From the available literature, we concluded that incorporating multiple perturbation types and directions might be of most benefit [28]. Each training session will therefore incorporate platform (translations and tilts in the forward, backward, left and right direction) and treadmill perturbations (unilateral treadmill belt accelerations and decelerations) during standing and walking. Each perturbation type has seven increasing difficulty levels (Tables 4, 5 and 6). For each subject, the first training session will be started with perturbations of each type on level 1. Difficulty levels will then be increased based on individual training progression and NRS scores.

#### Training procedures

The first training session on the CAREN system will start with a period of familiarization, where the subject can get used to the system by walking on the treadmill. Subjects will report an NRS score for how comfortable they feel walking on the CAREN before and during familiarization (0; very uncomfortable to 10; fully comfortable). If a score of 7 or higher is reached, familiarization is complete. We expect that this will occur within 6–7 min [45].

After this, each subjects’ comfortable walking speed will be determined using a ramped protocol; the walking speed will start at 0.5 m/s and will gradually be increased until the subject says ‘stop’ when they think their comfortable walking speed is reached. The subject will walk at this speed for approximately 1 min to check if any adjustments need to be made.

The consecutive sessions will start with a warming-up during which the subject will walk on the treadmill for approximately 3 min on a level surface and readjust to the system. Each training session will consist of three parts: gait adaptability, static reactive balance, and dynamic reactive balance. Training difficulty can be progressed by increasing the perturbation magnitude and walking speed. During the second and final training sessions, cognitive and motor dual tasks can also be added to increase training difficulty. Training adherence will be monitored throughout the study, and subjects will be encouraged to reschedule any missed training sessions.

#### Gait adaptability

Subjects will walk in a virtual environment on a path through a forest, with various slopes and turns. Both the incline/decline of the slopes and the sharpness of the turns will have a standardized starting level of 20% (out of 100%), which will then be progressed in steps of 5 to 15%. A difficulty level of 20% corresponds to a maximum incline/decline and rotation of 2 degrees. Each 5% increase in difficulty level means an increase in the maximum incline, decline and rotation of 0.5 degrees. For the percentage by which the difficulty level will be increased for each NRS score, see Table 3.

#### Static reactive balance

Subjects will stand on the CAREN while the platform and treadmill make sudden movements. The platform can shift or tilt to anterior, posterior, left and right. The treadmill belt can unilaterally accelerate from standstill. All possible perturbations have seven difficulty levels (see Tables 4, 5 and 6). Training will start at level 1 for each subject.

#### Dynamic reactive balance

Subjects will walk on the treadmill at their comfortable walking speed, while the above mentioned platform and treadmill perturbations are applied. The treadmill perturbations will consist of unilaterally accelerating or decelerating the treadmill belt for short periods of time, simulating a trip or a slip, respectively (Table 6).

### Outcomes

#### Balance control (main outcome)

The main outcome in this study is balance control, which will be measured with the Mini Balance Evaluation Systems Test (Mini-BESTest). The Mini-BESTest has been identified as the most comprehensive measurement tool to assess balance in community-dwelling older adults [46]. It measures balance in four categories: proactive balance, reactive balance, sensory orientation and dynamic gait. Each of the 14 tasks is scored on a three-point scale, with a total score that can range from 0 to 28 points. A higher score corresponds with better balance control. Proactive balance is tested using a sit-to-stand transfer where the subject has to try not to use their hands, standing on tiptoes, and standing on one leg. Reactive balance is tested with therapist-applied lean-and-release perturbations in the forward, backward and sideways directions. Sensory orientation is tested by standing with feet together, standing with feet together and eyes closed on a foam surface, and standing on a slope with eyes closed. Dynamic gait is tested with five tasks; suddenly changing gait speed, walking while turning the head left and right, walking and turning, stepping over an obstacle while walking, and Timed Up and Go performance. The Mini-BESTest has good psychometric properties [47, 48]. Cut-off values indicating increased fall risk for the Mini-BESTest are age dependent; ≤25 points for people 60 to 69 year of age, ≤23 points for 70 to 79 years, ≤22 points for 80 to 89 years and ≤ 17 points for 90 years and older [49]. The minimal detectable change on the Mini-BESTest is 3.5 points and the minimal important change is 4 points [47]. Balance control will be measured at baseline, T_1_ and T_2_.

#### Retrospective falls incidence

At baseline, the number and circumstances of falls during the past year of each subject will be recorded. A fall is defined as ‘an event which results in a person coming to rest inadvertently on the ground or floor or lower level’ [50]. We will use an adapted version of the ‘falls history questionnaire’ as presented in the book *‘Falls in older people: risk factors and strategies for prevention’* [51]. This questionnaire records if a fall has occurred in the previous period (12 months), where it has happened, what the perceived cause was, and if and what kind of injuries were sustained. The outcome assessor will fill in this questionnaire together with the subject to make sure that the recorded data is as comprehensive and clear as possible.

#### Prospective falls incidence

From the moment of inclusion, the prospective falls incidence of each subject will be monitored for up to 8 months (the potential training period + 6 months) post baseline. The prospective falls incidence will be monitored with falls diaries and questionnaires. The falls diary is a calendar that the subject will fill in at the end of each day. They are instructed to put an ‘X’ if they did not fall that day, or a number representing the number of times they fell during that day. At the end of each month, subjects will fill in the falls history questionnaire about that particular month, and send this back to the researchers in pre-addressed and pre-paid envelopes. If a fall incident is reported, the researcher will follow this up with a short phone call to elaborate on the circumstances and consequences of this fall. If a calendar has not been returned within 10 working days after the end of the month, the researcher will remind the subject with a phone call. A final follow-up will take place at 2 years post-baseline, where the researcher will check each patients’ EPR, to see if there were any more hospital visits due to injurious falls.

#### Fear of falling

Fear of falling will be measured with the Falls Efficacy Scale International (FES-I, Dutch version). This version of the falls efficacy scale is a 16-item questionnaire developed to determine if a person has confidence in their ability to perform a range of daily activities without falling. It has been adapted to be more suited to older adults, including a range of activities from very basic to more complex [52]. The questionnaire will be filled in by the subject with the help of the outcome assessor. Sixteen items are scored on a four-point [1–4] scale, with a maximum score of 64 points. A higher score corresponds with a greater fear of falling. The Dutch version of the FES-I has good reliability and validity and discriminative power in older adults [52–55]. Fear of falling will be measured at baseline, T_1_ and T_2_.

#### Acceptability of the intervention

This study will evaluate not only the effect but also the acceptability of the intervention. In a sub-sample of the intervention group, semi-structured interviews will be conducted to investigate the acceptability of the PBT protocol. Each of these subjects will be interviewed once (for approximately 30 min) after completing the intervention. The interview guide will be based on the TFA, which consists of seven subsections:
Affective attitude: how does the subject feel about the intervention, what is their opinion about it?Burden: did participating in the intervention take (a lot of) effort in terms of exertion or balance?Ethicality: did the intervention fit the subject’s previous views on falls prevention?Intervention coherence: did the subject understand the goal(s) of the intervention and how it works?Opportunity costs: did the subject have to give up other opportunities to take part in the intervention (e.g. cancel other appointments)?Perceived effectiveness: did the subject notice any effects (physical or otherwise) of the intervention, during training or after their participation?Self-efficacy: how confident was the subject about their ability to participate in and complete the intervention?

Two interviewers will be present at each interview; one will lead the interview, while the other will observe non-verbal communication, make notes, and help keep track of the interview guide. In addition to the framework, any perceived barriers/facilitators to participating in the intervention will be discussed. The interviews will take place at MUMC+ and will be administered by the research staff who are familiar with the training protocol.

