**Methods:**

This is a mixed-methods study combining a single-blind (outcome assessor) randomized controlled trial (RCT) using a parallel-group design, and qualitative research evaluating the acceptability of the intervention. The study sample consists of community-dwelling older adults aged 65 years and older who have recently fallen and visited the MUMC+ outpatient clinic. Subjects are randomized into two groups. The control group (*n* = 40) receives usual care, meaning referral to a physical therapist. The intervention group (*n* = 40) receives usual care plus three 30-min sessions of PBT in the Computer Assisted Rehabilitation Environment. Subjects’ balance control (Mini-BESTest) and fear of falling (FES-I) will be assessed at baseline, and 4 weeks and 3 months post-baseline. Daily life falls will be recorded with falls calendars until 6 months after the first follow-up measurement, long-term injurious falls will be recorded at 2-years’ follow-up via the electronic patient record. Acceptability of the PBT protocol will be evaluated with semi-structured interviews in a subsample from the intervention group.

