While the body of evidence for the effectiveness of PBT for falls prevention is growing, there are other factors to consider [8, 32, 34–36, 39–41]. The perturbations applied in these studies are of such a magnitude that they may not be acceptable to all older adults. Even the most effective interventions are likely to fail if they are not acceptable to the target population. Therefore, the literature recommends combining quantitative and qualitative methods to assess both the effectiveness and acceptability of a new intervention [42]. In this study, we will assess the acceptability of our training protocol through semi-structured interviews, utilizing the definition and theoretical framework of acceptability (TFA) described by Sekhon et al. [43].

This study protocol describes a mixed-methods study combining an outcome-assessor blinded randomized controlled trial (RCT), using two parallel groups (1:1) and a superiority design, with qualitative research concerning the acceptability of the intervention. The primary aim is to determine the effect of our three-session PBT intervention on balance control measured with the Mini-BESTest in community-dwelling older adults (≥65 years) who visit the outpatient clinic after a fall, in comparison to usual care. Secondly, we aim to determine the effect on real-life falls incidence during a 6 months follow-up period. We will also evaluate the effect on fear of falling measured with the Falls Efficacy Scale International (FES-I). A long-term follow-up evaluation will take place at 2 years post-baseline when each subjects’ electronic patient record (EPR) will be checked with the aim of investigating the long-term effect of PBT on injurious falls.

Lastly, we aim to determine the acceptability of our three-session PBT protocol through semi-structured qualitative interviews in a sub-group of the intervention group in this study.

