### Sample size

Sample size was calculated in G*power 3.1.9.2 and was based on the primary outcome of this study, difference between means on balance measured with the Mini-BESTest at T_1_. The effect size *d* (0.61) was calculated based on values from an article with a similar study population and an intervention aimed at improving dynamic balance control [56]. We assumed that our control group would remain stable as they receive no extra training aimed at balance improvement. Sample size was based on a one-tailed independent samples t-test, an α of 0.05, power (1-β) of 0.80 and allocation ratio of 1. This results in a required sample size of *n* = 72. Accounting for an expected loss to follow-up of 10%, the final sample size is *n* = 80. Sample size was estimated conservatively, making no assumptions about the correlation between predictors (group allocation and baseline score) added into the model and the outcome variable.

For the purpose of investigating the acceptability of the PBT protocol, a sub-sample from the intervention group will be included. The sample size will be based on the concept of theoretical saturation as described by Glaser & Strauss [57]. If there are two consecutive interviews that provide no new information, no new interviews will be planned. We expect to include approximately 15 subjects for the interviews.

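### Acceptability interviews are timed after completion of the training, with no stated route for subjects who stop early, so their views could be missed

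*Protocol article*

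**What the plan says.** The Background gives the reason for studying acceptability: "The perturbations applied in these studies are of such a magnitude that they may not be acceptable to all older adults". It adds that even an effective intervention is likely to fail if its target population does not accept it.

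Under Outcomes, the section Acceptability of the intervention names the source of interviewees: "In a sub-sample of the intervention group, semi-structured interviews will be conducted to investigate the acceptability of the PBT protocol". The next sentence sets the timing: "Each of these subjects will be interviewed once (for approximately 30 min) after completing the intervention". The interview guide covers seven framework domains, including burden, affective attitude, opportunity costs and self-efficacy. It also goes beyond the framework: "any perceived barriers/facilitators to participating in the intervention will be discussed".

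The Sample size section sets the number of interviews by saturation: "If there are two consecutive interviews that provide no new information, no new interviews will be planned". It then gives the expected total: "We expect to include approximately 15 subjects for the interviews".

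On attendance, Training procedures says: "Training adherence will be monitored throughout the study, and subjects will be encouraged to reschedule any missed training sessions". No section says what happens with the interview when a subject stops after one or two of the three sessions.

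**The concern.** The only interview time point applies to every interviewee and lies after completion. A subject who gives up the training never reaches it. Whether someone completes is likely to depend in part on the domains being studied: burden, fear and confidence in being able to finish. Tying the interview to completion therefore risks selecting interviewees on a consequence of acceptability.

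The saturation rule cannot reveal the gap. Two consecutive interviews with nothing new, both with completers, show that completers' views have been covered. They say nothing about a group that was never asked.

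At stake is the acceptability aim. The Strengths section intends the acceptability findings to support further development and use in clinical practice, where some patients may not finish the programme. The Weaknesses section does not mention this limit. The randomized comparison, the primary outcome and its analysis are not affected.

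**Working it through.** **Figure in the plan.** The expected 15 or so interviews rest on saturation. No formula is given, so there is nothing to reproduce.

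**Reading the sections together.**

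- Sampling frame (Acceptability of the intervention; Sample size): a sub-sample of the intervention group. Completion is not listed as a criterion.
- Timing (Acceptability of the intervention): once, after completion, for each interviewee.
- Route for subjects who stop (Background, Training procedures, Acceptability of the intervention, Sample size, Statistical analysis): none stated.

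The frame admits subjects who stop, but the timing gives them no interview. Followed to the letter, the two together yield completers only.

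**How often would sampling regardless of completion reach someone who stopped?**

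Inputs from the article: intervention arm N = 40 (Abstract, Methods); interviews n = 15 (Sample size, approximate). Assumed, because the article gives no rate of stopping: k = 2, 4, 6 or 8 subjects stop (5%, 10%, 15%, 20%). Also assumed: a simple random sample of fixed size, which saturation sampling only approximates.

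Expected number among the 15 = 15 × k / 40.

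P(at least one) = 1 − C(40 − k, 15) / C(40, 15).

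For k = 2 this is 1 − (25 × 24) / (40 × 39) = 1 − 600/1560 = 0.615.

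| k stopping | Expected among 15 | P(at least one), regardless of completion | P(at least one), literal wording |
|---|---|---|---|
| 2 | 0.75 | 62% | 0 |
| 4 | 1.50 | 86% | 0 |
| 6 | 2.25 | 95% | 0 |
| 8 | 3.00 | 99% | 0 |

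This needs no assumption about what those subjects think. With k = 0 nothing is lost.

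**Direction of any distortion.** Let q be the share who stop, a the share of completers who find PBT acceptable, and b the share of those who stop who do. The completers-only view exceeds the whole-arm view by a − [(1 − q)a + qb] = q(a − b). All values are assumed, with a = 90%:

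| q | b = 0% | b = 50% | b = 90% |
|---|---|---|---|
| 5% | 4.5 points | 2 points | 0 |
| 10% | 9 points | 4 points | 0 |
| 20% | 18 points | 8 points | 0 |

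The difference disappears if those who stop think as completers do. The table shows direction only, since the trial plans no such proportion.

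**The case against.** The strongest reply is that the sentence fixes when the interview happens, not who is eligible. The sampling frame is the intervention group, and no exclusion of subjects who stop is written. The phrase could simply mean after the training period. A condensed article may also leave the selection of interviewees to the full protocol. This stands as far as it goes: a reader might infer that subjects who stop are excluded by rule, and the article does not say so. But the timing condition is itself stated and, followed literally, has that effect.

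A reader might also infer that acceptability will be overstated. The documents do not support that as a result. They give no rate of stopping PBT; the 10% in Sample size is expected loss to follow-up for the trial, not discontinuation of training. The outcome is a content analysis with no acceptability proportion to inflate.

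Other mitigations are real but partial. Completers can report burden and barriers, and finishing is not the same as approving. Individualized difficulty and rescheduling of missed sessions may keep stopping rare. Adherence is monitored and adverse events are recorded, so non-completion is not invisible. However, the article does not say that adherence monitoring records reasons for stopping, and barriers are discussed only with those interviewed.

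**Conclusion.** The point holds as a matter of wording with a plausible consequence. Every interview is timed after completion, no route is given for subjects who stop early, and a literal reading confines both the interviews and the saturation judgement to completers. The group that bears most directly on the concern in the Background could go unheard.

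The size depends on how many stop and why, and the article gives neither. On the assumed 2 to 8 subjects stopping out of 40, sampling regardless of completion would usually reach at least one (62% to 99%), against none under the literal wording. A more favourable picture is the likely direction if some stop because they find the training unacceptable. There is no distortion if nobody stops or if those who stop hold the same views. The change is worth making because it is cheap, not because a bias has been shown.

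**What to change.** 1. In Acceptability of the intervention, change the interview timing to after completing or stopping the PBT sessions.
2. Invite subjects who stop early as part of the planned sub-sample of about 15. The saturation rule need not be held open until every such subject has been invited.
3. Report interviewees by completion status, next to the adherence data already collected. This also keeps the mix visible: if 10 of the 40 stopped and all were among 15 interviewees, they would be 10/15 = 67% of the interviews but 10/40 = 25% of the arm.
4. If no subject who stopped can be interviewed, limit the acceptability conclusions to completers and say so among the limitations.

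The cost is one change of wording and a few interviews, mostly within the number already planned. The Trial status section describes recruitment as ongoing, so the change could still be applied to interviews not yet held. The main drawback is that some who stop may decline. Randomization, the training itself and the quantitative analysis are unchanged.
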